### Study organization

#### Data collection and outcomes

We will collect blood samples of patients to test leukocytes, neutrophils, and inflammatory factors. Sample collection will be performed by trained nurses. Samples will be sent to the Department of Laboratory Medicine immediately after collection. The laboratory evaluation will be conducted by technicians, who will be blinded to treatment groups. Laboratory results will be placed in an electronic chart. Specimens will be destroyed and not stored for any ancillary studies. Preoperative data will be collected within 3 days after recruitment. Surgery data will be collected within 2 days after operation. Postoperative data will be collected within 3 days after discharge. For patients discharged home, we will conduct follow-up information by phone calls and these data will be recorded within 3 days after follow-up. If there are any errors or omissions in the electronic chart, the investigator will correct them immediately. The raw data will be marked clearly when revising and will be signed by the investigator with date when the modifications are made. All data can be obtained only by the study researchers who have signed the confidential disclosure agreement.

#### Complications

Some postoperative complications, such as bleeding, pain at the incision site, postoperative air leak, prolonged air leak, and atelectasis, will be treated in accordance with clinical guidelines. During every ward round, conducted at least twice a day, the doctors in charge will solicit the patients’ feedback and perform specific physical examinations to monitor any adverse events. All adverse events will be recorded in a timely fashion in the CRF. Postoperative follow-up will be conducted for all participants. Participants with any serious harm experienced as a result of trial participation will receive adequate compensation.

#### Primary and secondary outcomes

All outcomes will be defined in accordance with two previous studies [17, 18]. The primary outcomes are the levels of leukocytes, neutrophils, and inflammatory factors—interleukin-1β (IL-1β), IL-6, IL-8, IL-2, tumor necrosis factor-alpha (TNF-α), C-reactive protein (CRP), prostaglandin E_2_ (PGE_2_), and 5-hydroxytryptamine (5-HT)—on the first postoperative day. On the first postoperative morning, a trained nurse will collect blood samples and then send samples to test. The mean difference of the levels of leukocytes, neutrophils, and inflammatory factors will be compared between the two groups.

The secondary outcomes are (i) the levels of leukocytes, neutrophils, and inflammatory factors (IL-1β, IL-6, IL-8, IL-2, TNF-α, CRP, PGE_2_, and 5-HT) on the second and third postoperative days; (ii) the incidence of postoperative fever on the first, second, and third postoperative days; (iii) the volumes of chest drainage within the first 3 operative days, the duration of drainage, and postoperative hospitalization; and (iv) the incidence of postoperative complications (incision infection, pain, atelectasis, hemorrhage, etc.) and the incidence of pleural effusion requiring thoracic puncture or drainage within 30 days after surgery.

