### Sample size

This is the first study that focuses on the effect of different volume of pleural lavage on the clinical outcomes following VATS lobectomy and MLND, and no reference is available to estimate the sample size. We estimated the power on the basis of the Student’s *t* test of the levels of leukocytes on the first postoperative day in each group. We estimate an effect size of 0.5 from our experience. A total of 400 participants will be recruited in this study (200 in each group). Judging from our experience, we set the dropout rate at 10% to account for inability to complete the treatment, data errors, loss to follow-up, and other unanticipated study problems. Given a type I error rate of 5%, this study could provide a power of 99.72% by using G*Power (software version 3.1.3, University of Düsseldorf, Germany).

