### Statistical analysis

The main content of the analysis consists of effectiveness analysis and safety analysis. The analysis of all continuous variables will be presented as mean, standard deviation (SD), median, quartile spacing, and maximum and minimum values. The analysis of all dichotomous variables will be presented as rate, constituent ratio, and hazard ratio. We will use the *t* test and chi-squared test, analysis of variance, and univariate and multivariate logistic regression analysis to describe our data. The factors (*P* <0.15) in univariate analysis will be analyzed in multivariate analysis. All data will be checked twice by two independent statisticians. The two independent statisticians will also be blinded to treatment assignment. We will perform post-hoc subgroup analysis to identify potential significant factors based on age, sex, tumor location, clinical stage of tumor, resection scope, duration of surgery, the volume of intraoperative bleeding, and pathological stage of tumor. Demographics and clinical characteristics of the subjects are summarized as mean ± SD for continuous variables and as number (percentage) for categorical variables. The difference between groups will be considered statistically significant if the *P* value is less than 0.05. All data will be analyzed by using SPSS (software version 25.0; SPSS Inc., Chicago, IL, USA).

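### Ten equally ranked primary markers, no success rule and a flat P<0.05, while the planned 5% error and 99.72% power belong to one leukocyte test

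*Protocol article*

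**What the plan says.** Four statements in the protocol article bear on this.

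- **Primary and secondary outcomes (endpoint set).** "The primary outcomes are the levels of leukocytes, neutrophils, and inflammatory factors", measured on the first postoperative day. The inflammatory factors are listed by name, and the same eight recur under the secondary outcomes: "inflammatory factors (IL-1β, IL-6, IL-8, IL-2, TNF-α, CRP, PGE_2_, and 5-HT". Leukocytes, neutrophils and these eight make ten primary markers.
- **Primary and secondary outcomes (comparison).** "The mean difference of the levels of leukocytes, neutrophils, and inflammatory factors will be compared between the two groups". No marker leads, there is no order of testing, and no rule says how many must differ or in which direction.
- **Statistical analysis.** "The difference between groups will be considered statistically significant if the" P value is below 0.05. No multiplicity procedure is mentioned here or elsewhere in the article.
- **Sample size.** Power rests on a Student's t "test of the levels of leukocytes on the first postoperative day in each group". The effect size is a judgement: "We estimate an effect size of 0.5 from our experience". There are 200 patients per group and 10% dropout is assumed. The result reads: "Given a type I error rate of 5%, this study could provide a power of 99.72" per cent.

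**The concern.** The Sample size section describes a trial with one primary test. The outcome and analysis sections describe a trial with ten primary tests, each judged against the full 5%. Nothing connects the two.

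The gap matters because the abstract expects the findings to settle how much lavage fluid is appropriate, and the Conclusion hopes for a standardised procedure. As written, if lavage volume had no effect on any marker, a single chance result among ten could still be reported as a positive primary finding. Markers moving in opposite directions could be read either way. The investigators are not blinded to allocation, which is a further reason to settle the rule before any data are seen.

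**Working it through.** **Inputs from the protocol article:** 10 primary markers (2 cell counts + 8 factors); threshold 0.05; 200 per group; 10% dropout, so 200 × 0.9 = 180 per group; effect size 0.5, given for leukocytes only and read as a standardised mean difference d. Sidedness is not stated; two-sided is used because it reproduces the stated figure.

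**Step 1. Reproduce the stated power.** For a two-sample t test with n per group, the noncentrality is d × √(n/2) and the degrees of freedom are 2n − 2.

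- With n = 180 and d = 0.5: noncentrality 0.5 × √90 = 4.74, df = 358.
- Power at two-sided 0.05 from the noncentral t distribution: **99.72%**, an exact match.
- Alternatives do not match: 99.88% with no dropout (n = 200), 99.90% with a one-sided test at n = 180.

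The arithmetic is right. It describes one test at the full 5%.

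**Step 2. Error if any one of the ten suffices.** Under independence: 1 − 0.95^10 = **40.1%**.

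The article gives no correlations between markers, so the values below are assumptions. They come from simulating ten normal test statistics with a common correlation (400,000 draws) and counting how often at least one exceeds 1.96 in absolute value.

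| Assumed common correlation | Chance of at least one false-positive primary |
|---|---|
| 0 | 40% |
| 0.3 | 35% |
| 0.5 | 29% |
| 0.7 | 21% |
| 0.9 | 13% |

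**Step 3. If all ten must succeed.** Requiring every test to reach 0.05 does not inflate the type I error. Power changes instead. If d = 0.5 held for every marker (an assumption), power at 180 per group would be 0.9972^10 = 97.2% under independence, rising to 99.1% at correlation 0.9. Neither is 99.72%.

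**Step 4. Power with the error controlled.** Holm tests the smallest P value at 0.05/10 = 0.005, so power at 0.005 is a lower bound for each marker under Holm. With 180 per group:

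| d | Power at two-sided 0.005 |
|---|---|
| 0.5 (stated, leukocytes only) | 97.2% |
| 0.4 (assumed) | 83.3% |
| 0.3 (assumed) | 50.9% |

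The first row may be quoted for leukocytes. For the other nine markers the protocol gives no effect size, so no single figure can be quoted.

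**The case against.** **The error claim is conditional.** A reader might call the ten markers co-primary and conclude that the trial has a 40% false-positive rate. The documents support neither step. Co-primary normally means that all endpoints must succeed, and that does not inflate the error; the protocol does not use the word and states no rule of either kind. The 40% needs both an any-of-ten rule and independent markers. Neutrophils are themselves part of the leukocyte count, so at least that pair is unlikely to be near independent, and 40% is best seen as the top of the range. This objection stands and sets the form of the conclusion.

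**The power statement is honest about its scope.** The section says openly that it rests on the leukocyte test and takes the 5% as an input. It never claims 99.72% for all ten markers. That also stands: nothing is miscalculated, and a reader who infers an arithmetic error would be wrong. What remains is that the article gives no power figure for the primary analysis it defines.

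**A separate analysis plan may set the adjustment.** This is the strongest defence. A named procedure is often left to that plan, and a threshold of 0.05 could be applied to adjusted P values. The absence of a named procedure would not by itself be a finding. But the protocol itself fixes ten equal primaries beside a flat threshold and a one-test power basis. An adjustment added later would still leave the success rule open unless that were also stated, and would change the stated power.

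**Conclusion.** The point holds in conditional form. The protocol fixes ten undifferentiated primary markers, no lead endpoint, no success rule and P below 0.05 without multiplicity control, while its planning figures belong to one leukocyte t test.

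- If any one marker is enough, the family-wise error lies between about 13% and 40% across assumed common correlations from 0.9 down to 0. Even the low end is more than twice the 5% used in planning.
- If all ten are required, the error is not inflated, but 99.72% is not the power of that analysis.

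The main defect is error control and the missing decision rule. It is not the number of patients: for leukocytes at d = 0.5, power stays at about 97% even at the 0.005 level. That reassurance does not extend to the other nine markers, because the protocol gives d = 0.5 for leukocytes only.

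**What to change.** **Preferred.** Name the day-1 leukocyte level, the only powered endpoint, as the single primary outcome, tested at two-sided 5%. Move the other nine day-1 markers to secondary. The stated 99.72% then stands unchanged. The cost is wording in the protocol and, where it lists the same outcomes, the registration. No further patients are needed, and the Trial status section says recruitment had not opened. The nine markers lose primary status.

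**Alternative.** Keep ten primaries, control the overall error at two-sided 5% with Holm, and write down the success rule, including how markers moving in opposite directions will be read. Restate power as conditional on effect size. At the 0.005 level with 180 per group it is at least 97% for leukocytes at d = 0.5. For the other markers, whose effect sizes are not given, show a range such as 83% at d = 0.4 and 51% at d = 0.3. The cost is a lower stated power, and for markers with smaller effects the planned 400 patients may not be enough.

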### Protocol amendments

The current protocol is version 1.0 (September 25, 2018). Any amendment to the protocol that may affect the process of study or the benefits and risks to participants will require the agreement of the ethics committee.

## Discussion

It is essential to flush the thoracic cavity before chest wall closure. However, scant data could be found in the literature. The most frequently used method is to flush the thoracic cavity with 0.9% sodium chloride injection heated nearly to the temperature of the human body at 38~40 °C. No determinant criteria on volume of pleural lavage fluid have been built. If the volume of pleural lavage is too small, the residual tumor cells and tissue cannot be washed away, which may result in increased absorption of inflammatory mediators, fever, and even severe inflammatory reactions and will affect prognosis and prolong hospital stay. Furthermore, the residual tumor cells may increase the risk of recurrence and metastasis. If the volume of pleural lavage is too high, it will cause waste of resources and prolongation of operation time.

The study will enroll 400 NSCLC patients undergoing VATS lobectomy and MLND and divide them into two groups. This study aims to find out whether different volumes of pleural lavage fluid (0.9% sodium chloride injection) have different effects on prognosis of NSCLC patients measuring by some important clinical indices such as the plasma levels of leukocytes, neutrophils, inflammatory factors, and the incidence of fever after operation were observed 1 to 3 days after operation.

However, the study has some limitations. First, it is a single-center trial, which will restrict its generalizability, so a multiple-center large-sample clinical trial is warranted in the future. Second, the anesthesiologist and surgeons in charge of the intraoperative part of the study cannot be blinded to this study group regarding the safety. Third, the hospitalization time may be different across participants, which may bring effects on the prognosis of patients with NSCLC. Fourth, larger patients may need different volumes of pleural lavage.

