## Background

In pulmonary surgery, pleural lavage is routinely performed before closing the chest wall, to rinse off residual tumor cells and tissues and ideally prevent pleural implantation of tumor and postoperative infection [1]. Decades ago, it was known that even if there were no obvious malignant pleural effusion or pleural implants, tumor cells could be found in as much a third of postoperative pleural lavage [2]. Since then, accumulating data have indicated the presence of tumor cells in intraoperative pleural lavage as an independent prognostic factor [3–5]. Intraoperative pleural lavage cytology detected before closure could present a higher prognostic value than pleural lavage cytology detected before thoracotomy. Furthermore, it could guide the choice of adjuvant chemotherapy for lung cancer patients after surgery.

Although there is no guideline regarding how pleural lavage should be conducted [6], usually it involves irrigating the thoracic cavity with 0.9% sodium chloride injection varying from 20 to 2000 mL [2, 7–9] at 38~40 °C [10]. However, there are no determinant criteria on the volume of pleural lavage fluid. If the volume of pleural lavage is too small, the residual tumor cells and tissue cannot be washed away, which may result in increased absorption of inflammatory mediators, fevers, and even severe inflammatory reactions [11]. It could affect prognosis and prolong hospitalization [12]. Furthermore, the residual tumor cells may increase the risk of recurrence [13] and metastasis [14–16]. If the volume of pleural lavage is excessive, it will cause waste of resources and prolongation of operation time. Kaneda et al. [9] found that doses of over 500 mL could cause false-negative results of pleural lavage cytology. Considering clinical practice and the literature [7, 8], we decided to test two volumes of pleural lavage: 500 and 3000 mL.

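### Longer operation time is the cost the protocol names for too much lavage, but it is not a listed outcome, and duration of surgery appears only as a subgroup factor

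*Protocol article*

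**What the plan says.** **Rationale.** The Background states: "If the volume of pleural lavage is excessive, it will cause waste of resources and prolongation of operation time". The Discussion repeats it: "If the volume of pleural lavage is too high, it will cause waste of resources and prolongation of operation time". For too small a volume, the Discussion names residual tumor material, "which may result in increased absorption of inflammatory mediators, fever, and even severe inflammatory reactions", a longer hospital stay, and a possible rise in recurrence and metastasis.

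**Claim.** The discussion paragraph of the Abstract says the results will settle the right amount of lavage before closure. The Conclusion, more cautiously, says the trial may help to standardize the procedure.

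**Outcomes.** Under Primary and secondary outcomes: "The primary outcomes are the levels of leukocytes, neutrophils, and inflammatory factors", ten blood measurements in all, on day 1. The secondary outcomes are the same measurements on days 2 and 3, fever, "the volumes of chest drainage within the first 3 operative days, the duration of drainage, and postoperative hospitalization", "the incidence of postoperative complications (incision infection, pain, atelectasis, hemorrhage, etc" and similar events, and effusion needing puncture or drainage within 30 days. The Abstract gives the same list. Neither list contains operation time.

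**Duration of surgery.** It appears once, under Statistical analysis, among the post-hoc subgroup factors: "tumor location, clinical stage of tumor, resection scope, duration of surgery, the volume of intraoperative bleeding, and pathological stage of tumor". The section on data collection says that surgery data are recorded within two days of the operation, without listing the variables.

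**The concern.** The article gives a reason against too little fluid and a reason against too much. It plans to measure inflammation, fever and stay, which belong to the first reason. It does not list operation time, the measurable part of the second. If the larger volume lowered a marker, the report could show that gain without a planned estimate of the time it cost, and still be read as having settled the right amount.

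Duration of surgery is also given an unsuitable role. Patients are randomised before surgery and the lavage is done just before closure, so a duration measured to closure contains the intervention. The protocol itself expects volume to change it. Subgroups formed on such a variable are partly formed by allocation, and within them the arms are no longer comparable by randomisation.

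**Working it through.** **1. The plan's own figure.** Inputs from Sample size: 200 per arm, 10% dropout, effect size 0.5, type I error 5% (sidedness not stated). Analysed per arm: 200 × 0.9 = 180. For a two-sided two-sample t test, the noncentrality is 0.5 × √(180/2) = 4.74 on 358 degrees of freedom, and the power is 99.72%. This matches the article. The sample size is not in dispute, and 180 per arm is the basis for what follows.

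**2. Named consequences against listed outcomes.**

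| Named in Background and Discussion | Attached to | Listed outcome? |
|---|---|---|
| Inflammatory mediators and reactions | too little | yes, ten blood measurements |
| Fever | too little | yes |
| Longer hospital stay | too little | yes |
| Recurrence, metastasis | too little | no |
| Longer operation | too much | no |
| Waste of resources | too much | not directly; stay is an indirect measure |

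Drainage volume and duration, complications and effusion are also compared, and each can favour either arm.

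**3. What the existing sample would give for operation time.** The article states no SD for operating time, so the SDs here are assumptions. The 95% CI half-width for a difference in means is 1.96 × SD × √(2/180) = 1.96 × SD × 0.1054.

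- Total duration, SD 30 min: ±6.2 min
- Total duration, SD 50 min: ±10.3 min
- Start of lavage to chest closure, SD 5 min: ±1.0 min

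With all 200 per arm, the multiplier √(2/200) is 0.1, giving ±5.9 and ±9.8 min for total duration.

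The difference detectable with 80% power at two-sided 5% is (1.960 + 0.842) × 0.1054 = 0.295 SD. That is 8.9 min at SD 30 and 0.295 × 50 = 14.8 min at SD 50. At SD 30, the power to detect a true 5-minute difference in total duration is about 35%.

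**4. Reading.** Total duration needs no added patients and probably no added data item, but it is coarse for a step that may last minutes. Time from start of lavage to closure isolates that step and would be much more precise.

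**The case against.** The strongest case on the other side has five parts.

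- **The aim is not stated as a balance.** The Study objective speaks of effects on perioperative outcomes, and the Discussion of clinical indices such as markers and fever. Operation time is only rationale. This stands: a reader might infer that the trial undertakes to weigh benefit against operating time, and no section commits it to that. What remains is the mismatch between the named cost, the outcome list and the Abstract's broad claim.
- **The outcomes are not one-sided.** A reader might infer that the trial can detect only harm from too little fluid. It cannot be put that way. Drainage, stay, complications and effusion could show an advantage for either arm, and stay is an indirect resource measure. Nor are all harms of too little lavage covered, since recurrence and metastasis are not outcomes.
- **Some of the cost is known by design.** The arms differ by 3000 − 500 = 2500 mL of saline, so that material cost needs no outcome. True, but it says nothing about time.
- **Duration of surgery may be summarised anyway.** Statistical analysis promises descriptive statistics for all continuous variables, which arguably covers it. So one cannot say that it will never be shown by arm, only that it is not a pre-specified outcome.
- **Collection is inferred.** No list of recorded variables is shown. That duration of surgery is recorded follows from its use as a subgroup factor and from the statement that surgery data are collected. Time from lavage to closure would be a new item.

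The article also mentions false-negative cytology above 500 mL. No lavage cytology is described for this trial, so its absence from the outcomes is not part of this point.

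**Conclusion.** The point holds in a limited form. The protocol twice names longer operation time as a consequence of too much lavage and claims to settle the right amount, yet operation time is not a listed outcome. Its one related variable is assigned to subgroup analysis, where allocation can affect it. The gap is confined to that named cost.

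The primary comparison, its error rate and its power of 99.72% are unaffected. A pre-specified comparison would give the difference in total duration to about ±6 to ±10 min, or in lavage-to-closure time to about ±1 min. These figures rest on 180 analysed per arm and on assumed SDs of 30 to 50 min and 5 min. The subgroup point assumes that duration of surgery runs to closure and so contains the lavage; the article does not define it. This is a worthwhile, inexpensive improvement rather than an error that invalidates the trial.

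**What to change.** 1. Under Primary and secondary outcomes, add as a secondary outcome the between-arm mean difference, with 95% CI, in duration of surgery and in time from start of lavage to chest closure. Define the start and end of each.
2. Under Statistical analysis, remove duration of surgery from the subgroup factors.
3. If operation time is not added, limit the Abstract's concluding claim to the inflammatory and postoperative outcomes that are measured.

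Cost: one more secondary outcome to report and one clock time to note in theatre. No extra patients are needed and the primary analysis does not change. Trial status says that recruitment had not opened, so the new item could be recorded from the first patient.
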